## Ethics and dissemination

The current study received ethics approval from the Institutional Review Board (IRB) of Korea University Anam Hospital (2015AN0083).

## Discussion

The novelty of this study lies in its comprehensive examination of all the parts within the pathway of blood flow from mother to fetus. The rationale behind this study design stems from the objective to investigate the pathophysiology of fetal growth within the clinically observable range of ultrasonography, encompassing the processes that involve UtA, uterine wall, placenta, UV and fetal growth, The aim is to elucidate the pathophysiology of fetal growth. Through this study, we aim to find the association between new ultrasonographic indices, including UV absolute flow, and placental and uterine wall thickness and perinatal outcome of growth restricted fetuses. As it is significant to distinguish growth restricted fetuses with adverse perinatal outcomes from the constitutionally small fetuses, we posit that this study may contribute to the identification of new risk factors or the development of a prediction model for genuinely growth restricted fetuses in future study. By evaluating and comparing the various ultrasonographic uteroplacental-fetal biometric measurements and Doppler indices according to fetal growth, we can determine how much each ultrasonographic index influences fetal growth. Through this finding, we can provide evidence for future studies on the pathophysiology of FGR fetuses. Lastly, we can also assess the distribution of umbilical vein flow values according to estimated fetal weight in each trimester of pregnancy.

There are some possible limitations of this study. Firstly, because this is a multicenter cohort study, the quality of ultrasound examinations may vary from center to center. However, because in all participating hospitals, the ultrasonography is performed only by obstetricians, we posit that a certain degree of quality control measures could be instituted. Secondly, the lack of long-term outcomes on FGR fetuses is another limitation of the study. Thirdly, the lack of information regarding contraction at the time of measurement is another limitation of the current study. The presence or absence of uterine contractions can affect the measurement of the uterine wall thickness. However, because of the inherent limitation of retrospective study, we consider that accurately determining the presence or absence of contractions at the time of measurement is unfeasible. Lastly, because the uteroplacental-feta Doppler waveforms are not usually measured in a routine perinatal check of fetuses with normal EFW, a certain degree of missing values is anticipated within the context of this study. To address this aspect, a large-scale prospective cohort study will be necessary in the future.

Current studies have mostly focused on the UA or MCA, and even though large-scale multicenter Doppler studies have been conducted, there is no general consensus on the optimal timing for the delivery of compromised FGR fetuses. This study may lay the foundation for future studies to suggest the optimal timing for the best perinatal outcomes of FGR fetuses.

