## Methods

### Study design and population

The U-AID study is a multicenter retrospective cohort study which is led by an obstetric ultrasonography research society of Korean Society of Ultrasound in Obstetrics and Gynecology (KSUOG). This is conducted in 13 academic hospitals in the Republic of Korea. This study includes singleton pregnant women who undergo fetal ultrasound during routine antepartum surveillance. The eligible participants are pregnant women over 19 years old who can understand information about the current study and make decisions on whether to voluntarily participate in the study. There is no limitation on gestational age but pregnant women with fetuses found to have structural anomalies, abnormal insertion of umbilical cord, chromosomal abnormalities, or any kind of congenital infection will be excluded. The abnormal insertion of umbilical cord includes velamentous insertion and marginal insertion of umbilical cord. Of note, pregnant women with missing value of UV flow, placental thickness, and uterine wall thickness will be excluded.

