### Exclusion criteria

Pregnant women with missing value of UV flow, placental thickness, and uterine wall thicknessPregnant women with fetuses with possible structural anomalies or abnormal insertion of umbilical cord found on ultrasoundPregnant women with fetuses with chromosomal abnormalitiesPregnant women who are proven to have an intrauterine infectionPregnant women who have limited data on clinical characteristics related to pregnancy and perinatal outcome

In this study, we define FGR as a status where both of the following 2 conditions are met; (1) an EFW or AC below the 10th percentile for gestational age during the second or third trimester of pregnancy and (2) birthweight below the 10th percentile for gestational age [3]. The INTERGROWTH-21^st^ growth chart is used for biometry and birthweights [21]. The FGR group includes both early-onset FGR and late-onset FGR. The control group includes participants with a fetus whose EFW and AC are in the range of 10^th^ to 90^th^ percentile for gestational age. The control group will be selected through 1:1 matching based on age, parity, and presence or absence of preeclampsia. The clinical information and U-AID indices of pregnant women who delivered between March 2016 and March 2023 will be extracted from the medical records.

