### Ultrasonographic uteroplacental-fetal biometrics and Doppler (U-AID) indices

We will collect the ultrasonographic uteroplacental-fetal biometric measurements and U-AID indices listed in Table 1 in each trimester of pregnancy. During the first trimester of pregnancy, we will collect ultrasonographic measurements from 11^0/7^ to 13^6/7^ weeks of gestation. The measurements will be assessed from 18^0/7^ to 23^6/7^ weeks of gestation during the second trimester of pregnancy and from 30^0/7^ to 36^6/7^ weeks of gestation during the third trimester of pregnancy. The ultrasound model used and the clinical experience years of clinicians who measure U-AID indices will also be documented. To assess fetal growth, crown to rump length, biparietal diameter, head circumference, abdominal circumference, femur length, and estimated body weight will be evaluated. UA Doppler which was measured in a free cord loop and MCA Doppler which was measured in the proximal third of the MCA will be selected. The systolic/diastolic ratio (S/D ratio), pulsatile index (PI), and resistive index (RI) in the UtA, UA, MCA, and UV will be calculated as reported previously [22, 23]. The Doppler indices will be calculated as follows.

S/D ratio = peak systolic velocity [cm/sec] (S)–end-diastolic velocity [cm/sec] (D)PI = S–D / mean of S and D (M)RI = S–D / SNotch index = early diastolic flow velocity [cm/sec]/ peak diastolic flow velocity [cm/sec]UV absolute flow [ml/min] = UV cross-sectional area [cm^2^] * UV mean velocity [cm/sec] * 60

**Table 1 pone.0298060.t001:** Ultrasonographic uteroplacental-fetal biometric measurements and Doppler indices of the U-AID cohort.

**Uteroplacental-fetal biometry**	**Timing of measurement**	**Unit**
Crown to rump length	First trimester	Mm
Biparietal diameter	Second trimester, Third trimester	cm
Head circumference	Second trimester, Third trimester	cm
Abdominal circumference	Second trimester, Third trimester	cm
Femur length	Second trimester, Third trimester	cm
Estimated fetal weight	Second trimester, Third trimester	g
Placental thickness	Second trimester, Third trimester	mm
Uterine wall thickness	First trimester, Second trimester, Third trimester	mm
**Uteroplacental-fetal Doppler**		**Indices**
Uterine artery	First trimester, Second trimester, Third trimester	S/D ratio, PI, RI, early diastolic notch index
Umbilical artery	Second trimester, Third trimester	S/D ratio, PI, RI
Middle cerebral artery	Second trimester, Third trimester	S/D ratio, PI, RI

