### Statistical methods

The distribution of U-AID indices according to AC, BPD, EFW and gestational age will be assessed. The study population will be divided into two groups, the FGR group which includes participants with FGR fetuses, and the control group includes participants with normal growth fetus. First of all, we will compare the differences in U-AID indices according to adverse perinatal outcomes with in FGR group. Secondly, the difference of U-AID indices between the two groups will be compared. Continuous variables will be presented as the mean ± standard deviation or median [interquartile range] and compared by the Mann-Whitney U test or independent t-test according to the distribution of each variable. Categorical variables will be presented as the number of observations (percent) and compared by the chi-squared test or Fisher’s exact test. To determine the contribution of all the collected variables and Doppler findings to adverse perinatal outcomes of the FGR fetuses, multivariable logistic regression analysis with backward stepwise elimination will be used.

All statistical analyses will be performed using IBM SPSS statistics version 23.0 (SPSS Inc., Chicago, IL, USA) and R version 4.2.1 (http://www.r-project.org).

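### Index comparisons across 13 hospitals use tests with no centre term, and hospital is not a matching factor, so centre measurement differences can pass for index differences where centre mix differs between groups

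*Protocol article*

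**What the plan says.** All of the following is in the protocol article.

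- **Setting (Study design and population).** "This is conducted in 13 academic hospitals in the Republic of Korea". The data are existing records.
- **Control selection (paragraph after the Exclusion criteria list).** "The control group will be selected through 1:1 matching based on age, parity, and presence or absence of preeclampsia". Hospital, machine and operator are not on the list.
- **Machine and operator (section on U-AID indices).** "The ultrasound model used and the clinical experience years of clinicians who measure U-AID indices will also be documented". No analysis is said to use them specifically.
- **Index comparisons (Statistical methods).** Indices are compared by adverse outcome within the FGR group, and then: "Secondly, the difference of U-AID indices between the two groups will be compared". Continuous indices are "compared by the Mann-Whitney U test or independent t-test according to the distribution of each variable". No centre term or stratum is attached to either comparison.
- **Adjusted model (Statistical methods).** Adverse outcomes in FGR fetuses also go into a multivariable logistic regression over all collected variables, with backward elimination. It does not cover the FGR-control comparison.
- **Limitation (Discussion).** The article grants that "the quality of ultrasound examinations may vary from center to center". Its reply is that obstetricians do every scan, so "we posit that a certain degree of quality control measures could be instituted".

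**The concern.** A two-sample test compares group means over whatever mix of hospitals each group happens to have. If hospitals read an index systematically higher or lower, and one group draws more heavily on the high-reading hospitals, the difference in mix enters the group difference and the test cannot separate the two. For FGR versus control, this needs only a different centre mix in the two groups. Within FGR, it needs hospitals to differ both in how they measure and in how often adverse outcomes occur.

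The plan gives some reason to expect unequal mixes. The Discussion says Doppler is not usually recorded when estimated weight is normal, and women lacking UV flow, placental thickness and uterine wall thickness are excluded. Controls can then come only from places that recorded these in normal pregnancies. If that habit differs by hospital, which is an inference and not stated, controls will concentrate in some centres. Matching on age, parity and preeclampsia does not correct this.

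At stake are false associations, or masked true ones, for indices the study puts forward as new markers. An obstetrician-only rule does not remove differences between machines or in case mix.

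**Working it through.** The plan states no figure for centre effects, so there is none to reproduce. The size has to be explored over assumed values.

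**Inputs from the protocol article:** 13 hospitals; 525 FGR and 525 control women; base FGR number 472; alpha 0.05 (taken as two-sided).

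**Assumed inputs, not in the documents:**
- The share of index variance due to centre (ICC) is 0.02 to 0.20. A between-centre SD of 0.5 within-centre SDs corresponds to 0.25 / (1 + 0.25) = 0.20.
- Each group's centre mix is drawn independently from a Dirichlet distribution with parameter a = 20 (mild imbalance) or a = 5 (moderate imbalance). The mean centre share is 1/13 = 7.7%. The SD of a share is √[(1/13)(12/13)/(13a + 1)], which is 1.6 percentage points for a = 20 and 3.3 for a = 5.
- Within FGR: 25% adverse outcomes, between-centre measurement SD of 0.2 to 0.5 within-centre SDs, and centre log-odds SD of 0.3 to 0.8.

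**1. FGR versus control, closed form.** Scale the total SD to 1.
- Squared standard error used by the pooled test: 2/525 = 0.00381.
- Expected squared difference in centre mix: S = 2 × (12/13) / (13a + 1). For a = 5, S = 1.846/66 = 0.0280. For a = 20, S = 1.846/261 = 0.00707.
- Extra variance that the test ignores: S × ICC.
- Type I error ≈ 2 × [1 − Φ(1.96/√R)], with R = 1 + S × ICC / 0.00381.
- ICC 0.20, a = 5: R = 1 + 0.00559/0.00381 = 2.47, √R = 1.571, 1.96/1.571 = 1.247, error ≈ 21%.
- ICC 0.20, a = 20: R = 1 + 0.00141/0.00381 = 1.37, √R = 1.171, 1.96/1.171 = 1.674, error ≈ 9%.

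**2. FGR versus control, simulation.** No true difference, 2,000 runs per setting.

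| ICC | Pooled t-test, a = 20 | Pooled t-test, a = 5 | Centre fixed effect (a = 20; a = 5) |
|---|---|---|---|
| 0.02 | 5.6% | 7.0% | 5.2%; 5.0% |
| 0.05 | 6.1% | 8.9% | 5.0%; 4.9% |
| 0.10 | 7.2% | 12.6% | 4.4%; 4.9% |
| 0.20 | 8.8% | 21.9% | 5.1%; 5.3% |

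The Monte Carlo standard error near 5% is √(0.05 × 0.95/2000) = 0.5 percentage points, so the top left entry cannot be told from 5%. The simulation agrees with the closed form (21.9% against 21%, 8.8% against 9%).

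When both groups have the same number of women from each centre, the pooled t-test rejects in 2.7% to 5.2% of runs over ICC 0.02 to 0.20. There is no inflation, and the test is conservative at high ICC.

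**3. Within FGR, simulation.** No true association, 472 women, equal expected centre sizes, 4,000 runs per setting.

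| Between-centre measurement SD | Centre log-odds SD | Pooled t-test |
|---|---|---|
| 0.2 | 0.3 | about 5% |
| 0.3 | 0.5 | about 7% |
| 0.5 | 0.8 | about 13% |

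With centre in the model, the error returns to about 5%.

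**The case against.** **This is a condensed article, and centre handling may sit in a fuller plan.** This stands in part. The article neither includes nor rules out a centre term, and recording machine and experience fits an intention to use them. It also does not say outright that controls are drawn across hospitals. But the tests and the matching factors are written out, and hospital appears in neither. The point concerns a stated method, and the Discussion raises the centre problem without offering an analytic answer.

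**A reader might infer that the primary question is analysed without any adjustment.** The documents do not support that. The logistic model addresses adverse outcomes in FGR over all collected variables, and machine and experience could enter it. Elimination also tends to keep strong terms. What remains is that centre is not named and no term is protected.

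**A reader might infer that pooling 13 hospitals invalidates the tests by itself, or that ultrasound quality is known to differ.** Neither follows. With a shared centre mix there is no inflation. The article says only that quality may vary, and it fixes one UV flow formula and one measurement site for the thicknesses, which limits some of the variation.

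**A reader might expect FGR-control error rates above 30%.** These arise only under strong imbalance, such as a = 2 with a between-centre SD of 0.5, where a rerun gave 34%. Groups drawn from the same 13 hospitals would probably have correlated mixes, and so less inflation than independent draws suggest.

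**Conclusion.** The concern holds in limited form. It bears most on the FGR-control comparison, which is secondary and has no adjusted analysis in the article, and on the univariable within-FGR comparison. It bears less on the logistic model, where the gap is an unnamed and unprotected centre term.

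The plausible cost ranges from negligible to a false-positive rate of two to four times nominal: about 13% within FGR and about 20% for FGR versus control at the upper end of the assumed settings. These rates depend on the assumed ICC, centre mix and event rate, and should be read as illustration, not as estimates for this study. The direction does not depend on them: if centres measure differently and the groups differ in centre mix, the pooled tests absorb the difference and a centre-adjusted comparison does not. The change is worth making because it is cheap, not because serious bias has been shown.

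**What to change.** 1. In Statistical methods, replace the pooled tests as the main index comparison, both FGR versus control and by adverse outcome within FGR, with centre-adjusted differences. Use a linear model with centre as fixed effect or random intercept or, for skewed indices, a rank test stratified by centre.
2. Force centre into the logistic model for adverse outcomes and exempt it from elimination. A random intercept is the more sparing choice if events are few.
3. Use ultrasound model and operator experience, already being recorded, as covariates in a sensitivity analysis.
4. Optionally, select controls within hospital. This also removes the inflation, so it is an alternative to item 1 for the FGR-control comparison and not an added requirement. It changes control selection, and some FGR women may have no match.

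Items 1 to 3 need no new data, since the hospital of each record is known in a chart review. A fixed centre effect uses 13 − 1 = 12 degrees of freedom, small against 1,050 women. The rest is a little more analysis work.
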